### Enteropathy substudy

The sample size was estimated using previously reported values for LM ratios, which remain a widely used non-invasive marker of enteropathy. Comparing 100 versus 100 children with two-sided alpha=0.025 (to allow for two primary comparisons, ie, HIV-SAM vs HIV-negative children with SAM, and HIV-SAM vs well-nourished HIV-positive children) provides >80% power to detect differences in mean LM ratio during hospitalisation of at least 0.16 (assuming SD 0.36), a difference which would be clinically relevant given the LM ratios previously reported for well-nourished children (0.42), malnourished children (1.3) and children with persistent diarrhoea (2.85) in the Gambia.^60^ It also provides >80% power to detect differences of at least 0.1 in the mean change in LM ratio from enrolment (assuming SD for change=0.23 and 7% missing samples). For inflammatory markers, comparing 100 versus 100 children with two-sided alpha=0.025 provides >80% power to detect differences in mean log_10_ concentrations of at least 0.44 times their SD, or 2.75-fold differences between groups. Inclusion of well-nourished controls provides an indication of normal ranges in young African children. HIV-positive and HIV-negative SAM groups will be stratified to include approximately 50 children with and without oedematous malnutrition, if possible.

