## Study design

HOPE-SAM is a longitudinal observational cohort study, enrolling between 600–800 children aged 0–59 months admitted with complicated SAM to the tertiary paediatric wards at two sites in Zimbabwe (Parirenyatwa Hospital and Harare Children’s Hospital) and one in Zambia (University Teaching Hospital, Lusaka). Both HIV-positive and HIV-negative children will be enrolled. Throughout this paper, ‘SAM’ refers to all children, regardless of HIV status; where analyses specifically compare children by HIV status, groups are identified as HIV-positive children with SAM (HIV-SAM) and HIV-negative children with SAM. All participants with SAM are followed for 48 weeks post discharge, with longitudinal data collection and blood sampling. The study contains four nested substudies as shown in figure 1. A subgroup of children will be recruited to the enteropathy substudy for which they will have the same follow-up procedures but more intensive biological specimen collection including stool (all time points), urine after lactulose-mannitol (LM) challenge as an assessment of intestinal permeability and nasogastric aspirate (baseline only); these children are also included in microbiota and metabolomics substudies. Children with SAM for whom blood samples are available are included in the immunology substudy, for which circulating inflammatory mediators will be assayed; functional cellular immunology assays will be conducted for all children in the immunology substudy with sufficient sample volume (>2 mL) recruited after June 2017. A group of healthy children recruited from the same hospitals and communities, who are well-nourished and matched to children in the enteropathy substudy by age and HIV status, will have data and specimens collected to provide normative data for the laboratory substudies; these well-nourished controls will not be followed longitudinally.

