## Sample sizes

### Observational study

The observational cohort will recruit as many children with SAM as possible during the period of enrolment (July 2016 to March 2018), estimated at 600–800 children (capped at 800 maximum), to assess clinical and nutritional outcomes among HIV-positive and HIV-negative children hospitalised with SAM. Assuming mortality of 15%, overall loss to follow-up of 15% and recruitment target of 800 children, there would be 560 evaluable children at 48 weeks, of whom 224 would have HIV-SAM based on an estimated inpatient HIV prevalence of 40%. This will provide >80% power to detect absolute differences of 17% in binary outcomes between HIV-SAM and HIV-negative children with SAM, and of 0.33 times the SD in continuous outcomes.

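### The stated power of over 80% for change in LM ratio is about 76% at the alpha the text gives and holds only at an unstated alpha of 0.05; the 2.75-fold figure rests on an unstated SD

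*Protocol article*

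**What the plan says.** All the relevant figures are in the protocol article under Sample sizes.

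- **Basis of the calculation (Enteropathy substudy).** "Comparing 100 versus 100 children with two-sided alpha=0.025". The alpha is halved "to allow for two primary comparisons": HIV-SAM against HIV-negative SAM, and HIV-SAM against well-nourished HIV-positive children. The first result given is for mean LM ratio in hospital: a difference of 0.16 with SD 0.36.
- **Change in LM ratio (same paragraph).** The same sample is credited with power above 80% for this target: "differences of at least 0.1 in the mean change in LM ratio from enrolment (assuming SD for change=0.23 and 7% missing samples"). No new group size or alpha is given, and no follow-up visit is named.
- **Inflammatory markers (same paragraph).** With 100 against 100 and alpha 0.025, the detectable difference in mean log10 concentration is "at least 0.44 times their SD, or 2.75-fold differences between groups". No SD is given.
- **Attrition in the parent cohort (Observational study).** "Assuming mortality of 15%, overall loss to follow-up of 15% and recruitment target of 800 children", which leaves 560 evaluable at 48 weeks.
- **Controls (Study design).** "these well-nourished controls will not be followed longitudinally".

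**The concern.** The sentence on change follows directly from the one that sets 100 per group and alpha 0.025, so a reader takes those values as carried over. Allowing for 7% missing, they do not give the stated power. If the power is overstated, a null result for the difference in change between HIV-SAM and HIV-negative SAM would be read with slightly more confidence than it deserves.

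The sentence is also under-specified in two ways that affect the answer. Without a time point, the 7% cannot be set against the cohort's own attrition. And the reason for halving alpha does not carry over to change, because one of the two comparisons needs follow-up of controls that is not planned.

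The fold figure raises a different question. It treats a multiple of an SD and a fixed ratio as the same thing, which needs a particular SD that is not stated.

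**Working it through.** **Inputs.** 100 per group, two-sided alpha 0.025, difference 0.1, SD of change 0.23 and 7% missing (Enteropathy substudy); 15% deaths plus 15% loss (Observational study). 7% missing leaves 100 × 0.93 = 93 per group; 30% attrition leaves 70.

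**Method.** Two-sample t-test with noncentrality δ / (SD × √(2/n)) and 2n − 2 degrees of freedom. The normal approximation is given as a cross-check.

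**Step 1: reproduce the neighbouring figures (100 per group, alpha 0.025).**
- In-hospital LM ratio: 0.16 / (0.36 × √0.02) = 3.143. Power 81.1% (normal 81.6%). Reproduces.
- Inflammatory markers: 0.44 / √0.02 = 3.111. Power 80.2% (normal 80.8%). Reproduces.

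The method and alpha are therefore the ones the article used for those two figures.

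**Step 2: change in LM ratio, difference 0.1, SD 0.23.** At 93 per group the standard error is 0.23 × √(2/93) = 0.0337, and 0.1 / 0.0337 = 2.965.

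| Evaluable per group | Power, alpha 0.025: t (normal) | Power, alpha 0.05: t (normal) |
|---|---|---|
| 100 (none missing) | 79.2% (79.8%) | 86.4% (86.7%) |
| 93 (7% missing) | 75.9% (76.5%) | 83.9% (84.3%) |
| 70 (30% missing) | 62.1% (63.0%) | 72.4% (73.0%) |

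At alpha 0.025 the claim fails even with no missing samples. At alpha 0.05 with 7% missing it holds.

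**Step 3: detectable difference at 80% power.** The normal approximation is (z₁₋α/₂ + z₀.₈) × SD × √(2/n).
- 93 per group, alpha 0.025: (2.241 + 0.842) × 0.23 × √(2/93) = 0.104; the t version is 0.105.
- 70 per group, alpha 0.025: 0.12.
- 70 per group, alpha 0.05: 0.11.

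To hold 0.1 at alpha 0.025, the t-test needs 102 evaluable per group. With 7% missing that is 102 / 0.93 = 109.7, or 110 enrolled per group.

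**Step 4: the fold figure.** A difference of 0.44 SD in log10 concentration is a ratio of 10^(0.44 × SD). At SD = 1.0 this is 10^0.44 = 2.75, the printed value. The article gives no SD, so the following are assumed values to show the range:

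| Assumed SD (log10) | Fold difference at 0.44 SD |
|---|---|
| 0.3 | 1.36 |
| 0.5 | 1.66 |
| 0.8 | 2.25 |
| 1.0 | 2.75 |
| 1.2 | 3.37 |

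**The case against.** **Alpha 0.05 may have been intended.** Controls have a single assessment, so HIV-SAM against well-nourished HIV-positive children cannot be compared on change. One comparison remains, the reason for 0.025 lapses, and at 0.05 the claim is true. The Analysis section also says that p values will not be adjusted and that everything is exploratory. This stands as a justification for 0.05, but not as a reading of the text, which sets 0.025 and never departs from it. On this view the error is an unreported alpha, and the sentence still needs correcting.

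**The shortfall is slight.** A detectable difference of 0.104 to 0.105 rounds to the printed 0.1, and the planned analysis of change uses generalised estimating equations over several visits, for which a single-visit t-test is only a proxy. This bears on severity. The printed claim is still power above 80% for a difference of 0.1, and on its own inputs that is not reached.

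**A reader might infer that the true power is 62% and that 7% missing contradicts the cohort's 30%.** The article does not support that. The 30% applies at 48 weeks, while the sentence names no visit, and LM testing is also scheduled at discharge and week 12, where losses should be lower. Testing is deferred until a child is clinically stable, so some early deaths may precede the first test, and enrolment runs until enough specimens are collected. The 62% is a sensitivity figure for one possible reading. Nor should the HIV-specific inpatient mortality cited in the Introduction be used to go lower, since the sample size section does not adopt it.

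**A reader might also infer that 2.75-fold is wrong.** It is correct if the log10 SD is 1.0, and nothing in the article rules that out. With a smaller SD, smaller ratios are detectable and the figure is conservative; with a larger SD it is optimistic. That 2.75 is 10^0.44 suggests that SD units were read as log10 units, but this is inference.

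**Conclusion.** The power stated for change in LM ratio is wrong as written: about 76% at 100 against 100, two-sided alpha 0.025, SD 0.23 and 7% missing, and 79% with none missing. It becomes 84%, and the claim true, only at two-sided alpha 0.05, which is defensible for change but not stated. These figures rest on a two-sample comparison at one visit with equal losses in the two groups.

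Whether 7% missing is too low depends on the visit meant. It is in tension with the cohort's planning figures only if that visit is week 48.

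The 0.44 SD figure is correct. Its fold equivalent is unsupported, because it needs a log10 SD of 1.0 that the article does not state.

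The point is minor. The substudy is exploratory, enrolment of children with SAM has ended, the in-hospital LM calculation reproduces, and no sample size or analysis needs to change.

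**What to change.** - **Change in LM ratio.** State the alpha and the follow-up visit for this calculation. If 0.025 is kept, give 76% power with 7% missing, or a detectable difference of about 0.105. If 0.05 is adopted, give 84%, with the reason that controls are not followed and HIV-SAM against HIV-negative SAM is the only comparison of change.
- **Missing samples.** If change to 48 weeks is meant, reconcile the 7% with the 30% deaths plus loss in the observational cohort calculation, or explain why the substudy would lose fewer. As a sensitivity figure, 70 per group gives 62% power and a detectable difference of 0.12 at alpha 0.025, or 72% and 0.11 at alpha 0.05.
- **Inflammatory markers.** Keep 0.44 SD. State the log10 SD assumed for the markers, or replace the 2.75-fold figure with 10^(0.44 × SD).

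The cost is a few sentences. Under alpha 0.025, or with 48-week attrition, the stated figures become somewhat less favourable.

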### Microbiota and metabolomics substudy

Power calculations are difficult in metagenomics and metabolomic analyses due to the large number of observed outcomes and unknown effect sizes and variance. Previous studies using smaller sample sizes have identified significant taxonomic differences in twin pairs discordant for oedematous-SAM (n=13)^25^ and metabolic differences between the two forms of SAM (n=40).^26^ These studies suggest that a difference of 50% in metabolites could be expected. Using analysis of covariance, setting α=0.05 and assuming either low (ρ=0.1) or high (ρ=0.7) correlation, the study would require 95–126 subjects to achieve 80% power.^61^ False discovery rate multiple correction testing will be applied to reduce the high-dimensionality of the data and limit false positives.

### Immunology substudy

Up to 200 children with SAM and 200 well-nourished controls will be included in a cross-sectional analysis of innate immune cell function during hospitalisation. Assuming similar infectious mortality to a recent Kenyan study (15%),^17^ a cohort of 200 provides 80% power to detect associations between immune profiles and infectious mortality at an OR of 1.7 and two-sided alpha of 0.05. We will aim for 100 children with longitudinal analysis of innate immune cell function at discharge, 12, 24 and 48 weeks post discharge.^17^

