### Long-term outcomes of SAM

Following resolution of complications and return of appetite, children are discharged from hospital to continue therapeutic feeds at home. However, emerging data indicate high post discharge mortality following in-hospital management of SAM.^11–13^ Malnutrition, together with young age, HIV infection and pneumonia, has been associated with higher post discharge mortality.^14^ One of the largest prospective studies of growth and mortality in children with SAM (FuSAM), conducted in Malawi from July 2006 to March 2007, collected 12-month outcome data on 87% of 1024 children admitted to the nutrition ward.^11^ A total of 427 (42%) died and 44% of these deaths occurred after discharge from hospital. Survival was greatest among those who were nutritionally cured on discharge from outpatient therapeutic feeding centres, defined as two consecutive visits with >80% expected weight-for-height, no oedema and clinically stable. The risk of mortality after hospital discharge was fourfold higher for HIV-SAM compared with HIV-negative children with SAM, but the outcomes among HEU children were not reported. The loss to follow-up was high in the FuSAM study because there was only one follow-up visit, 1 year after discharge from outpatient-feeding centres. A recent study from Kenya identified malnutrition and HIV infection as key drivers for post discharge mortality, with 52% of deaths attributable to MUAC <11.5 cm and 11% to HIV infection.^15^

The impact of SAM appears to persist beyond the first year after discharge from hospital. The ChroSAM study, which followed children with SAM 7 years post discharge, showed that children had poorer growth, body composition and physical function compared with siblings and community controls, which are all indicators of future cardiovascular and metabolic disease.^12^

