### Immunology substudy

Integrated profiles of innate immune cell function will be generated for each child using principal components analysis followed by hierarchical clustering.^65 66^ This data -reduction method identifies whether absolute levels of specific markers or relative differences between markers differentiate children into groups. The resulting innate immune profiles will be compared between HIV-SAM, HIV-negative children with SAM and well-nourished groups using univariable tests and multivariable analysis of variance of the principal components.

To address the relationship between immune function and infections, regression analyses will determine whether baseline innate immune profiles (or the individual parameters defining them) are associated with the infectious morbidity or mortality during hospitalisation, using logistic models for binary outcomes and linear models for duration. Key clinical characteristics, including age, sex, oedema and baseline WHZ, will be added to models to investigate their confounding effects. Multivariable stacked regression methods will be used to compare the impact of different factors on severe bacterial infections based on heterogeneity tests.

To determine whether treatment for SAM restores innate immune cell antibacterial function, mixed effects regression models will compare longitudinal changes in individual immune parameters, and the principal components calculated from the weights identified at baseline (which include well-nourished controls). Similarities and differences in longitudinal immune profiles will be compared between groups using non-metric multidimensional scaling.^65 67 68^ This approach will group children according to their composite innate immune function, allowing the duration and variability of immune restoration to be evaluated over the course of nutritional rehabilitation. Binary logistic regression will determine whether innate immune profiles at discharge are associated with morbidity or mortality during follow-up.

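### The immunology substudy's 80% power rests on 15% infectious mortality, which does not fit the protocol's own all-cause mortality assumption or the in-hospital outcome it tests

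*Protocol article*

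**What the plan says.** Three sections of the protocol article bear on this.

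- **Sample sizes, Immunology substudy.** "Up to 200 children with SAM and 200 well-nourished controls will be included" in the in-hospital cross-sectional analysis. The event rate is borrowed: "Assuming similar infectious mortality to a recent Kenyan study (15" per cent). On that basis the section claims that "a cohort of 200 provides 80% power to detect associations between immune profiles and infectious mortality at an OR of 1.7" (alpha 0.05, two-sided). No time window is attached to the 15%.
- **Sample sizes, Observational study.** "Assuming mortality of 15%, overall loss to follow-up of 15" per cent too, 800 recruited children leave 560 evaluable at 48 weeks. Here the 15% is mortality from any cause.
- **Analysis, Immunology substudy.** Logistic models ask whether baseline profiles are "associated with the infectious morbidity or mortality during hospitalisation". Mortality during follow-up has a separate logistic analysis, based on discharge profiles.

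Two background sections give figures on when deaths occur. Under Long-term outcomes of SAM, the cited Malawi cohort had 42% mortality and "44% of these deaths occurred after discharge from hospital". The Introduction cites inpatient mortality of 30.4% in HIV-positive and 8.4% in HIV-negative children with SAM.

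**The concern.** The immunology children are drawn from the same cohort. Infectious deaths in hospital are a subset of all deaths up to 48 weeks, so both quantities can be 15% only if every death is infectious and none occurs after discharge. The protocol's own background contradicts this. A large share of deaths in the Malawi cohort came after discharge. The Kenyan trial that supplies the 15% is cited in the immunology substudy description for deaths following hospitalisation, which it describes as predominantly, not entirely, bacterial.

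At stake is how the immune-mortality result will be read. Power for an association with a binary outcome is driven by the number of events. If there are clearly fewer than the 30 deaths implied by 15% of 200, a null result could be taken as adequately powered evidence against an association when it is not.

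**Working it through.** **Inputs.** n = 200 (an upper limit), OR 1.7, two-sided alpha 0.05, infectious mortality p = 15% (Sample sizes, Immunology substudy). All-cause mortality 15%, HIV prevalence 40% (Sample sizes, Observational study). Share of deaths after discharge 44% (Long-term outcomes of SAM). Inpatient mortality 30.4% and 8.4% (Introduction). The unit of the OR is not given. I assume 1 SD of a continuous profile score, because a 50:50 binary profile would give only 26% power.

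**Formulae** (logistic regression on one standardised covariate):

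- Power = Φ( ln(OR) × √(n p (1−p)) − 1.96 )
- OR detectable with 80% power = exp( (1.96 + 0.842) / √(n p (1−p)) )

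**Reproducing the plan's figure.** At p = 0.15, √(200 × 0.15 × 0.85) = 5.05. Power = Φ(0.531 × 5.05 − 1.96) = Φ(0.72) = 76%; simulated logistic fits gave 73-77%. The OR detectable with 80% power is exp(2.802/5.05) = 1.74, which prints as 1.7. The plan's figure is therefore consistent with its inputs to rounding.

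**What the 15% means in the cohort calculation.** 800 × (1 − 0.15 − 0.15) = 560 evaluable at 48 weeks. The mortality term removes all deaths between enrolment and that visit.

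**Route A: cohort assumption with the Malawi split.** In-hospital share = 1 − 0.44 = 0.56, so all-cause in-hospital mortality = 0.15 × 0.56 = 8.4%, about 17 of 200. (This happens to equal the HIV-negative inpatient rate in the Introduction; the two are unrelated.) If every one of these deaths is infectious, √(200 × 0.084 × 0.916) = 3.92 and power = Φ(0.531 × 3.92 − 1.96) = 55% (simulation 52-57%). With an assumed infectious share of 60-90%, power is 37-51%. At 8.4%, 80% power needs about 363 children or an OR of about 2.04.

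**Route B: inpatient rates from the Introduction.** 0.40 × 30.4% + 0.60 × 8.4% = 17.2% all-cause in-hospital mortality.

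| Assumed infectious share | In-hospital infectious mortality | Power at OR 1.7 |
|---|---|---|
| 60% | 10.3% | 63% |
| 90% | 15.5% | 78% |
| 100% | 17.2% | 81% |

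Route B puts in-hospital deaths alone above the 15% that the cohort calculation allows for all deaths to 48 weeks, so the two cannot both stand.

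**Across event rates, n = 200:**

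| In-hospital infectious mortality | Power at OR 1.7 | OR detectable with 80% power |
|---|---|---|
| 15% | 76% | 1.74 |
| 10% | 61% | 1.94 |
| 8.4% | 55% | 2.04 |
| 5% | 37% | 2.48 |

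**The case against.** The best defence is that the low figure may be the cohort's 15%, not the immunology substudy's. The Malawi cohort had 42% mortality, so its split implies about 0.42 × 0.56 = 23.5% dying in hospital, and the Introduction's rates give 17.2%. If 15/17.2 = 87% of those inpatient deaths were infectious, the 15% would be right and the printed power would hold to rounding. This stands as far as it goes: the documents give no in-hospital infectious death rate, and they do not show which section is wrong. It does not remove the conflict, because the cohort assumption would then have to change.

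Four stronger readings are tempting, and the documents do not support them.

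- A reader might infer that true power is about 50%. That needs in-hospital infectious mortality near 7.4%, which no section states. It lies within Route A only, and Route B gives 63-81%.
- A reader might take the 76% as an arithmetic error. The detectable OR of 1.74 rounds to the printed 1.7, so it is not one.
- A reader might say the planned test counts only infectious deaths. It also covers infectious morbidity, which should supply more events, and follow-up mortality has its own discharge-profile analysis. The difficulty is confined to the power claim for mortality.
- A reader might call the missing OR unit a defect. A condensed article may leave that to the full protocol.

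It is also fair that all analyses are declared exploratory and that enrolment of children with SAM has ended, so the statement no longer governs recruitment. That limits the consequence to interpretation.

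**Conclusion.** The point holds as an inconsistency between the sample-size assumptions and the outcome analysed. Under the cohort's 15% all-cause mortality, infectious in-hospital mortality must be below 15%, and the claimed 80% power for mortality is unsupported. The size is conditional: at most about 55% if the Malawi timing of deaths applies to the cohort's 15%, and about 63-81% if the Introduction's inpatient rates apply. The second case requires the cohort's 15% to be revised upwards. These figures assume an OR per SD, one unadjusted continuous covariate, the full 200 children, and an infectious share of deaths (60-100%) that the documents do not give.

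**What to change.** 1. State the time window of the 15% infectious mortality, and reconcile it with the 15% all-cause mortality in the cohort calculation and with the in-hospital outcome in the immunology analysis.
2. Restate the mortality power conditionally, for example: *With 200 children and two-sided alpha 0.05, the OR per SD detectable with 80% power is about 1.74, 1.94, 2.04 or 2.48 if in-hospital infectious mortality is 15%, 10%, 8.4% or 5%.*
3. Optionally, add a supportive analysis relating baseline profiles to infectious death through 48 weeks with a cause-specific Cox model. Keep the planned logistic models: they pair baseline profiles with in-hospital outcomes and discharge profiles with follow-up outcomes, which is the question the substudy poses.

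Items 1 and 2 are changes of wording and need no new data. Item 3 would use deaths the study already records. Its small downside is that cause of death after discharge is less certain, since verbal autopsy is done only where possible.
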